## Abstract

**Objective:**

Full-thickness macular holes (FTMH) are defects in the fovea involving all neural retinal layers. They reduce patients’ visual acuity (VA) and impact their quality of life. FTMHs are repaired with pars plana vitrectomy (PPV) with intraocular gas tamponade and post-operative face-down positioning (FDP). There is no consensus regarding the ideal positioning requirements following FTMH repair and there lacks clear guidelines on the topic. While analysis of global practice patterns indicates that between 5–7 days is the most common duration suggested by surgeons, there is significant heterogeneity in surgeon preferences. There is, however, biological plausibility to support minimal or even no FDP following surgery and given the disabling nature of FDP for patients, there is a need to better assess key patient outcomes with different FDP durations. As such, this prospective randomized controlled pilot trial will compare 3-days of FDP to 7-days of FDP following PPV for FTMH.

**Methods:**

This single-centered, parallel-group randomized controlled pilot trial will randomize patients 1:1 following PPV to 3 days or 7 days of FDP. This investigation has been approved by the local ethics board (HiREB # 16100) and has been registered on clinicaltrials.gov (NCT06000111). The primary objective will be focused on assessing the feasibility of a larger trial; this will be determined through an assessment of the recruitment rate, retention rate, completion rate and recruitment time. The secondary outcomes involve assessment of the following patient-important outcomes a) macular hole closure rate, b) best-recorded VA, c) a general quality of life measure and vision-specific quality of life measure, d) patient compliance and e) complication rates. Outcomes will be evaluated at 3 months following surgery.

**Discussion:**

The results of this pilot study will determine the feasibility of a larger-scale trial that will answer a patient important question with clinical equipoise.

## Introduction

### Background and rationale

Full-thickness macular holes (FTMH) are defects in the fovea involving all neural retinal layers [1]. They reduce patients’ visual acuity (VA) and have a significant impact on patients’ quality of life [2]. Left untreated, patients experience progressive loss of central visual acuity [3]. The current standard of repair for FTMHs is pars plana vitrectomy (PPV) with or without peeling of the internal limiting membrane (ILM), the use of intraocular gas tamponade and post-operative face down positioning (FDP) [1, 3].

Face-down positioning (FDP) is the standard recovery posture for patients post PPV for FTMH. This however, can be physically challenging considering idiopathic FTMH occur most frequently in the elderly [4]. Previous investigations have demonstrated that over 50 percent of patients have described FDP as either difficult or very difficult [5, 6]. Moreover, rare but serious systemic complications such as pulmonary embolism or ulnar nerve palsies have been reported after FDP [7]. Consequently, suggestions have been made to reduce the duration of FDP or eliminate FDP completely [8, 9]. Presently, there is no consensus regarding the ideal positioning requirements following FTMH repair. A 2020 Preference and Trends Survey performed by the American Society of Retina Specialists (ASRS) and completed by 1273 retinal specialists from around the world demonstrated significant variability in current practices [10]. While the vast majority of surgeons recommend FDP, the duration of FDP varied considerably; the most frequently recommended duration was between 5–7 days of FDP (39.5% of responses) followed by 3–4 days (29.3% of responses).

There is, however, biological plausibility to support minimal or no FDP following surgery. The rationale for FDP is to ensure that the FTMH can be isolated from intraocular fluid thereby permitting subfoveal fluid absorption and closure of the FTMH [2, 11]. However, previous investigations have demonstrated that the first 24 hours is the most important period for isolating the FTMH from the intraocular fluid [2]. A large gas bubble even without FDP would be sufficient to achieve this [2]. In keeping with this, a recent meta-analysis of randomized controlled trials demonstrated no difference between FDP and non-FDP in FTMH closure [12]. In this investigation, there was a visual benefit to FDP however the confidence intervals included values of trivial clinical significance and there were serious concerns of imprecision. Consequently, the authors concluded that there is a need for a future large, well-conducted trial evaluating patient-important outcomes following FTMH repair [12].

Previous investigations evaluating the quality of life outcomes have demonstrated that patients prefer non-FDP; Veith et al. found that patients rated FDP as significantly more uncomfortable compared to non-FDP (p = 0.010) and that patients found FDP to significantly impair sleep quality (p = 0.001) [13]. Tadayoni et al. found that when they asked patients to rate the painfulness of positioning on a visual analog scale (0–10), pain was rated 6.52 ± 2.48 and 2.53 ± 2.6 in the FDP and alleviated positioning group respectively [7]. Patient preferences are also reflected by the fact that positioning compliance has been demonstrated to be lower in FDP groups compared to non-FDP [7], and by the fact that positioning compliance following PPV declines over time [14]. An investigation examining compliance during the first 3 days post-operatively found significantly decreased compliance each day after surgery [14].

Given the lack of guidelines on the topic, the corresponding heterogeneity in practice patterns, the lack of biologic rationale, and the disabling nature of FDP for patients, there is a need to better assess key patient outcomes with different FDP durations. As such, this investigation through a prospective randomized controlled pilot trial will compare 3-days of FDP to 7-days of FDP following PPV for FTMH. A pilot trial was deemed necessary to best assess the feasibility of a larger trial and to understand the resource and management requirements of the future larger-scale trial [15]. Pilot randomized trials are a type of feasibility study and are smaller-scale versions of the main study [16]. Pilot trials have been shown to increase the likelihood of a successful man trial and improve the methodology of the main study [15, 16].

The population examined in this investigation will be consecutive patients who present with an idiopathic FTMH to the Hamilton Regional Eye Institute. The intervention will be PPV with ILM peel followed by 3-days of FDP which will be compared to the control group undergoing PPV with ILM peel followed by 7-days of FDP. The primary outcome will be the feasibility of completing a larger-scale trial. Secondary outcomes will be focused on functional, structural, and quality-of-life outcomes. All outcomes will be examined at 3 months post-surgery.

### Objectives

Our primary objective will be focused on assessing feasibility. Feasibility will be assessed by measuring the recruitment rate, retention rate, and completion rate at 3 months following surgical repair as well as the recruitment time.

Our secondary outcomes will include a) macular hole closure rate at 3 months following surgery; two independent readers, masked to treatment allocation, will independently grade the outcome in each instance as closed, or open. Outcomes classified as open will be further divided into open and flat (without a cuff of subretinal fluid), or open and elevated (with a cuff of subretinal fluid). b) best-recorded visual acuity at 3 months post-surgery, c) compliance with FDP as assessed utilizing self-administered questionnaires four times per day during the duration of FDP, d) patient self-administered vision-specific validated quality of life measure, the 25-item National Eye Institute Visual Function Questionnaire (NEI VFQ-25) and a validated quality of life measure, the Quality of Life Scale (QOLS), and e) complication rates (endophthalmitis, retinal detachment, vitreous hemorrhage) as assessed by a masked physician.

The interpretation of findings will be: a) the full-scale trial is feasible with no changes to the protocol; b) the full-scale trial is feasible with small changes to the protocol; c) the full-scale trial is infeasible. The study will be considered feasible if the retention and completion rates are > 80% of randomized patients. The study will be considered feasible with small changes if either the retention or completion rate is <80% of randomized patients and the study will be considered infeasible if the completion and retention rates are <80% of randomized patients.

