**Methods: Participants, interventions, and outcomes**			
Study setting	9	Description of study settings (eg, community clinic, academic hospital) and list of countries where data will be collected. Reference to where list of study sites can be obtained	8
Eligibility criteria	10	Inclusion and exclusion criteria for participants. If applicable, eligibility criteria for study centres and individuals who will perform the interventions (eg, surgeons, psychotherapists)	8
Interventions	11a	Interventions for each group with sufficient detail to allow replication, including how and when they will be administered	8,13
	11b	Criteria for discontinuing or modifying allocated interventions for a given trial participant (eg, drug dose change in response to harms, participant request, or improving/worsening disease)	13,14
	11c	Strategies to improve adherence to intervention protocols, and any procedures for monitoring adherence (eg, drug tablet return, laboratory tests)	13,14
	11d	Relevant concomitant care and interventions that are permitted or prohibited during the trial	N/A
Outcomes	12	Primary, secondary, and other outcomes, including the specific measurement variable (eg, systolic blood pressure), analysis metric (eg, change from baseline, final value, time to event), method of aggregation (eg, median, proportion), and time point for each outcome. Explanation of the clinical relevance of chosen efficacy and harm outcomes is strongly recommended	6,7
Participant timeline	13	Time schedule of enrolment, interventions (including any run-ins and washouts), assessments, and visits for participants. A schematic diagram is highly recommended (see Figure)	16,17
Sample size	14	Estimated number of participants needed to achieve study objectives and how it was determined, including clinical and statistical assumptions supporting any sample size calculations	16
Recruitment	15	Strategies for achieving adequate participant enrolment to reach target sample size	17

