**Methods: Data collection, management, and analysis**			
Data collection methods	18a	Plans for assessment and collection of outcome, baseline, and other trial data, including any related processes to promote data quality (eg, duplicate measurements, training of assessors) and a description of study instruments (eg, questionnaires, laboratory tests) along with their reliability and validity, if known. Reference to where data collection forms can be found, if not in the protocol	15
	18b	Plans to promote participant retention and complete follow-up, including list of any outcome data to be collected for participants who discontinue or deviate from intervention protocols	15
Data management	19	Plans for data entry, coding, security, and storage, including any related processes to promote data quality (eg, double data entry; range checks for data values). Reference to where details of data management procedures can be found, if not in the protocol	15
Statistical methods	20a	Statistical methods for analysing primary and secondary outcomes. Reference to where other details of the statistical analysis plan can be found, if not in the protocol	18, 19
	20b	Methods for any additional analyses (eg, subgroup and adjusted analyses)	N/A
	20c	Definition of analysis population relating to protocol non-adherence (eg, as randomised analysis), and any statistical methods to handle missing data (eg, multiple imputation)	18, 19

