### Eligibility criteria

All consecutive treatment naïve patients with an idiopathic FTMH with a symptom duration of less than 6 months who agree to participate will be included in this investigation. Patients with macular hole minimum diameter >1000 μm, a history of high myopia (> -6), traumatic macular hole, amblyopia, retinal vein occlusion, inflammatory eye diseases, or who were found to have a retinal tear during either the pre-operative assessment or intraoperatively will be excluded.

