### Surgical technique

In both groups, patients will undergo standard three-port, 25-gauge PPV by one experienced retina specialist ([name]). If epiretinal membranes are present, they will be stained and peeled. The internal limiting membrane (ILM) will be stained with brilliant blue G dye and peeled as part of the surgical procedure. The size of the ILM peel will be approximately 1 disc diameter in radius and will increase proportionally to the size of the hole with larger peels performed for larger holes. Fluid-air exchange and a complete air-gas exchange will be performed utilizing sulfur hexafluoride (SF_6_ 18%) gas. The patients in both groups will be advised to posture face down immediately following surgery.

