### Data collection methods

After enrollment, patients will undergo standardized comprehensive ophthalmic examination including slit lamp examination, VA assessment, and measurement of intraocular pressure. VA will be measured with Snellen visual acuity with the patient’s corrective lenses with pinholing to minimize the effects of refractive error. Standardized examinations along with OCT (either the Cirrus HD-OCT, Carl Zeiss Meditec, Dublin Ca or the Heidelberg Spectralis OCT, Franklin, MA depending on the availability to the research assistant) will be performed within the 2-weeks before surgery and at the following post-operative times: 1-month, and 3-months. Patients will complete the NEI-VFQ-25 and the QOLS measures at baseline, and at 3-months following surgery. Compliance will be assessed utilizing a self-administered questionnaire in which patients will be asked to rate their compliance on a scale of 1–10 upon waking (to assess the overnight period), in the morning, at midday and in the evening. Complication rates, including rates of retinal detachment, endophthalmitis and vitreous hemorrhage will be assessed by a physician at the 1-week, 1-month, and 3-month follow-up assessments.

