## Discussion

There is a gap in the current literature evaluating the optimal duration of FDP following FTMH repair. This is evident by the heterogeneity in practice patterns, lack of clear guidelines, lack of biologic rationale, and imprecision in pooled estimates in meta-analysis on the topic [12]. Moreover, FDP can be disabling for patients; [12] patient values and preferences must be taken into consideration with the current evidence when making decisions in clinical practice [25]. There is a need for a large well-conducted randomized controlled trial evaluating key outcomes to surgeons and patients including patient-reported outcome measures.

Pilot trials are an underutilized method of assessing the feasibility of large, expensive full-scale studies and can greatly increase the likelihood of success as well as minimize potential sources of waste in the main trial [15, 16]. Moreover, a pilot trial will provide great insight into the resource and management requirements of the future larger-scale trial [15, 16].

The strengths of this protocol include the multiple measures introduced to limit potential sources of bias. Firstly, randomization will occur in permuted blocks of 4,6, and 8 to protect against selection bias. Individuals involved in identifying patients and obtaining consent will not be involved in the sequence generation of the randomization list. Additionally, a single highly experienced surgeon ([name]) will be performing PPV in both groups and will be masked to the patient’s treatment allocation at the time of surgery. While an element of bias is inevitable given that it will not be possible to blind patients to their allocation, we do not anticipate that this will affect our primary objectives of determining the feasibility of a larger-scale trial. Moreover, for the future main trial, the FTMH closure rate will be graded by two masked assessors and visual acuity will be assessed by a member of the research team masked to the patient’s treatment allocation. International experts in retinal diseases ranked FTMH closure rate and postoperative visual acuity as the two most important outcomes pertaining to FTMH repair [12]. Consequently, the proposed methodology ensures that all potential sources of bias pertaining to the assessment of these two outcomes are minimized. Lastly, analyses will be performed on an intention-to-treat basis to best preserve randomization and prognostic balance in study arms and minimize the type I error rate.

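### The 3-month visual acuity comparison is fixed as unadjusted and ignores lens status, which costs some precision and leaves a small-sample result open to chance imbalance

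*Protocol article*

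**What the plan says.** Objectives (Protocol article) names "b) best-recorded visual acuity at 3 months post-surgery" as a secondary outcome. Under Data collection methods, acuity is Snellen, taken with the patient's "corrective lenses with pinholing to minimize the effects of refractive error". Statistical methods and data analysis compares continuous variables between arms by t-test or Mann-Whitney test, depending on normality, by intention to treat and with 95% confidence intervals. No covariate is named, not even baseline acuity. In the SPIRIT checklist (Table 1), item 20b, "Methods for any additional analyses (eg, subgroup and adjusted analyses", is marked N/A. So is item 11d, "Relevant concomitant care and interventions that are permitted or prohibited during the trial".

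The lens is not mentioned. The ocular exclusions under Eligibility criteria, which include "a history of high myopia (> -6), traumatic macular hole, amblyopia, retinal vein occlusion, inflammatory eye diseases", do not refer to it. Surgical technique states that "Fluid-air exchange and a complete air-gas exchange will be performed utilizing sulfur hexafluoride" but does not say whether the eye has a natural or an artificial lens. The named complications are endophthalmitis, retinal detachment and vitreous hemorrhage. The randomization section gives block sizes and no stratification factor.

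Much of the needed information is nonetheless within reach. Before surgery and at 1 and 3 months, "patients will undergo standardized comprehensive ophthalmic examination including slit lamp examination, VA assessment, and measurement of intraocular pressure". Data management adds past ocular history to the findings of each examination.

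**The concern.** Eyes with natural and artificial lenses are mixed in one small comparison. The Introduction notes that idiopathic holes occur mostly in the elderly, so both kinds should be expected. A natural lens that clouds during follow-up lowers acuity, and a lens operation between visits can raise it, in neither case through the macular hole. That a lens may cloud after vitrectomy with gas is general clinical background and is not stated in the documents. Pinholing addresses refractive error, not opacity.

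The Discussion reports that experts rank postoperative acuity among the two most important outcomes of hole repair, so the pilot's acuity result will be read with interest. If lens findings are not recorded as such, nobody can later tell how much of the spread, or of any difference between arms, came from the lens. Because the article states the unadjusted tests and marks item 20b N/A, this is a choice the plan has fixed and not merely a detail left to a separate analysis plan.

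**Working it through.** **The plan's own figures.** It gives no sample size, power or SD for acuity. Its stated precision concerns feasibility and reproduces at n = 40:
- 1.96 × √(0.80 × 0.20 / 40) = 12.4 points
- 1.96 × √(0.33 × 0.67 / 40) = 14.6 points

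Neither bears on acuity.

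**Inputs from the documents.** 40 patients randomized 1:1, so 20 per arm. With 10% attrition, 36 are evaluable, 18 per arm.

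**Assumed inputs (none is in the documents).** Share with a natural lens p = 0.50–0.75; these eyes average δ = 0.1–0.2 logMAR worse at 3 months; residual SD 0.3 logMAR. Snellen values are assumed to be converted to logMAR.

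**1. Chance imbalance in lens status, 20 per arm.** SD of the difference in shares = √(2p(1−p)/20).
- p = 0.50: SD 0.158; probability of a gap of 20 points or more, 26.8%
- p = 0.75: SD 0.137; probability 19.9%

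**2. Resulting shift in the acuity difference (95% range).** 1.96 × SD × δ.
- δ = 0.1: ±0.027 (p = 0.75) to ±0.031 (p = 0.50)
- δ = 0.2: ±0.054 to ±0.062

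That is about 0.03–0.06 logMAR.

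**3. Added variance.** p(1−p)δ² / 0.3².
- δ = 0.1: 2.1% (p = 0.75) to 2.8% (p = 0.50)
- δ = 0.2: 8.3% to 11.1%

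Since √1.021 = 1.010 and √1.111 = 1.054, the standard error widens by about 1–5%.

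**4. Comparison with sampling error.** 95% half-width at 18 per arm: 1.96 × 0.3 × √(2/18) = 0.196 logMAR. The shift in step 2 is roughly 15–30% of that (0.03/0.196 to 0.06/0.196).

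**5. Price of the covariate.** Estimating one covariate raises the variance of the arm effect by roughly 1/(N−4), which is 1/32 = 3.1% at N = 36. At δ = 0.1 this cancels the 2–3% gain. At δ = 0.2, 1.031/1.083 = 0.95 and 1.031/1.111 = 0.93, so variance falls by about 5–7%.

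**6. Validity of the unadjusted test (simulation, 18 per arm, SD 0.3).**
- Lens clouding in 50% of both arms: rejection under no effect stays at about 5%. Power for a 0.2 logMAR difference falls from 49% with no lens effect to 46% (lens effect 0.2) or 41% (lens effect 0.3).
- Lens events in 60% of one arm and 40% of the other, with no macular effect: rejection rises to 6.6% (lens effect 0.2) or 8.5% (0.3). Nothing in the documents indicates such a difference between arms.

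**The case against.** The strongest reply is that an unadjusted comparison of a secondary outcome in a randomized pilot is valid as it stands. Allocation is concealed and made after surgery, so baseline lens status is balanced in expectation, and the p-value and confidence interval already allow for chance imbalance. Step 6 confirms this. The reply stands, and it limits the point to precision and interpretability.

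A reader might infer that lens change biases the acuity comparison and would be wrongly credited to positioning. The documents do not support that. False rejection rises only if lens events differ by arm, which is an assumption. If positioning itself altered the lens, the acuity change would be a genuine effect of assignment under intention to treat. A baseline covariate would not remove it, nor should it.

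A reader might also see a conflict with the Discussion's statement that "the proposed methodology ensures that all potential sources of bias pertaining to the assessment of these two outcomes are minimized". That sentence follows the description of masked graders and masked acuity assessors and concerns assessment. Prognostic variation between eyes is a different matter, so there is no contradiction.

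The remaining objections stand in part. The size of any lens effect is assumed throughout. Examination findings are already to be collected, so some lens data may exist without any change. Feasibility is judged on retention and completion, to which the acuity result does not contribute. None of this explains why a factor visible at a scheduled examination should be left out of both the named data items and the analysis.

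**Conclusion.** The point holds as an inexpensive improvement to a secondary analysis. The plan fixes an acuity comparison that uses neither lens status nor baseline acuity. At about 20 eyes per arm, under the stated assumptions, chance imbalance in lens status can move the between-arm difference by about 0.03–0.06 logMAR, and lens variation adds about 2–11% to the acuity variance, against a 95% half-width of about 0.20. The net precision gain from adjusting for the lens runs from near nil to about 5–7% of variance. Recording lens events also lets the acuity result be interpreted, whatever the size of their effect.

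The test is not invalid, no systematic bias has been shown, and the primary feasibility conclusions are unaffected.

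**What to change.** In Data collection methods and Data management, name lens status (natural or artificial lens; visually significant opacity yes or no) as an item recorded from the slit lamp examination at baseline, 1 month and 3 months, together with the date of any lens surgery.

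In Statistical methods and data analysis, replace the two-sample test for 3-month acuity with a regression on arm, baseline acuity and baseline lens status, reporting the adjusted difference and its 95% confidence interval. Change SPIRIT item 20b from N/A to match. Report lens surgery and visually significant opacity by arm descriptively.

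An analysis restricted to eyes selected by their 3-month lens findings should be left out or labelled exploratory, because it conditions on something that happens after randomization.

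The cost is a few REDCap fields completed from an examination already scheduled, and one or two degrees of freedom in a model with about 36 evaluable patients. No visit or procedure is added.

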### Sample size

The primary outcome of this investigation is to assess feasibility, as such, a power calculation to determine the sample size was not performed [15, 19, 20]. A literature review was undertaken to help inform the optimal sample size; no consensus was found with recommendations ranging from 24 to 50 described in the literature [21–23]. A previous RCT evaluating different positioning following PPV for FTMHs experienced a 10.2% attrition and thus we similarly estimate a 10% attrition rate in this investigation [24]. As such accounting for this attrition rate, utilizing a sample size of 40 patients, we will be able to estimate an 80% retention and completion rate to within a 95% confidence interval of +/-12.4% and a 33% recruitment rate to within a 95% confidence interval of +/- 14.6% [23]. We estimate based on previous rates of FTMH at our institution that there will be 3 new eligible patients each week. Previous studies at our institution have experienced a recruitment rate of 25%. Thus, we estimate that it will take approximately 53 weeks to achieve our target sample size.

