### Statistical methods and data analysis

Regarding the primary outcomes, the recruitment rate will be calculated as the number of patients randomized / the number of eligible patients screened. The retention rate will be defined as the number of patients who complete the follow-up measures at 3 months / the number of enrolled participants. Completion rates for data collection will be defined as the number of complete datasets for each of the outcome measures at 3 months / number of participants enrolled in the study. The recruitment time will be defined as the time taken in days to recruit 40 participants from the start of the enrollment period.

For the secondary outcomes, analyses will be performed on an intention-to-treat basis. Continuous variables will be expressed as means (± standard deviation) and categorical variables will be expressed as percentages. Continuous variables will be compared utilizing the student’s t-test or Mann-Whitney U test based on normality. Categorial variables will be compared utilizing the Chi-Squared Test. Fisher’s Exact Tests were performed for expected values less than five. A p-value of <0.05 will be considered statistically significant. All estimations will be reported with 95% confidence intervals. All analyses will be performed using R (version 4.3.1; R Foundation, Vienna, Austria).

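### Recruitment rate and recruitment time are two of the four primary feasibility outcomes, but no result for either can change the three-tier feasibility verdict

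*Protocol article*

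**What the plan says.** All references are to the protocol article.

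- **What determines feasibility.** The abstract's Methods paragraph says of feasibility that "this will be determined through an assessment of the recruitment rate, retention rate, completion rate and recruitment time". The Objectives section repeats the list, with the duration of recruitment as its last item: "Feasibility will be assessed by measuring the recruitment rate, retention rate, and completion rate at 3 months following surgical repair as well as the recruitment" [...].
- **Status and definitions.** Statistical methods and data analysis treats recruitment as primary: "Regarding the primary outcomes, the recruitment rate will be calculated as the number of patients randomized / the number of eligible patients screened". For time it says: "The recruitment time will be defined as the time taken in days to recruit 40 participants from the start of the enrollment period". Neither definition carries a threshold.
- **The verdict.** The Objectives section sets out three outcomes, starting with "The interpretation of findings will be: a) the full-scale trial is feasible with no changes to the protocol", followed by feasible with small changes and infeasible. The top tier is reached as follows: "The study will be considered feasible if the retention and completion rates are > 80% of randomized patients". The middle tier reads: "The study will be considered feasible with small changes if either the retention or completion rate is <80% of randomized patients". The bottom tier applies when both rates are below 80%.
- **Planning values.** The Sample size section expects 3 new eligible patients a week and says "Previous studies at our institution have experienced a recruitment rate of 25" per cent, from which it derives about 53 weeks. For the precision statement the same section uses a recruitment rate of 33%.
- **After the pilot.** Study timeline and status says that results will be reviewed and a decision taken on a future single-centre or multi-centre trial. It states no criterion.

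**The concern.** Feasibility is the trial's primary outcome, so the three-tier rule produces its primary conclusion. A rule that leaves out two of the four measures said to determine that conclusion contradicts the protocol's own list.

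It also leaves the verdict resting on the measures the protocol already expects to go well. It anticipates 10% attrition, against a threshold that tolerates just under 20%. The quantity with real uncertainty, whether enough eligible patients agree to take part and how fast, is measured but has no role in the verdict. A pilot that recruited several times more slowly than planned could be reported as showing that the full trial is feasible with no changes to the protocol.

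The article prints the rule in full, so this is not a detail left to an analysis plan that is not shown.

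**Working it through.** **1. Which measures enter the rule**

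| Measure | Declared as determining feasibility | Defined | Used in any tier |
|---|---|---|---|
| Recruitment rate | yes | yes | no |
| Retention rate | yes | yes | yes, against 80% |
| Completion rate | yes | yes | yes, against 80% |
| Recruitment time | yes | yes | no |

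The unqualified word feasible in the rule is read as the first tier (no changes). The order of the tiers and the separate rule for small changes support that reading.

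**2. The protocol's own recruitment time**

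Inputs from Sample size: N = 40, 3 eligible patients per week, recruitment rate r = 25%.

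Weeks = N / (3 × r) = 40 / (3 × 0.25) = 53.3. This reproduces the stated 53 weeks.

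**3. The same formula at other rates** (10% and 5% are assumptions)

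| r | Weeks to 40 | Multiple of plan | Verdict if retention and completion exceed 80% |
|---|---|---|---|
| 33% | 40 / 0.99 = 40 | 0.76 | feasible |
| 25% | 40 / 0.75 = 53 | 1.0 | feasible |
| 10% | 40 / 0.30 = 133 | 2.5 | feasible |
| 5% | 40 / 0.15 = 267 | 5.0 | feasible |

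**4. How easily the retention half is passed**

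With 10% attrition, true retention is 90%. Exceeding 80% of 40 means at least 33 retained: P(Bin(40, 0.90) ≥ 33) = 95.8%. This does not depend on recruitment speed. It covers retention only; completion must pass as well.

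**5. If recruitment simply stopped at the planned date**

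Study timeline and status gives 1 December 2023 to 31 December 2024, which is 396 days or 56.6 weeks. Reaching 40 in that window needs r = 40 / (3 × 56.6) = 23.6%. At an assumed 10%, about 3 × 56.6 × 0.10 = 17 patients would be randomized. The rule's denominator is randomized patients, so 14 of 17 retained with complete data (82.4%) would still be labelled feasible, with the target missed by more than half.

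**6. Where a recruitment cut-off could sensibly lie**

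Suppose the true values equal the plan (25%, Poisson arrivals at 3 per week, hence 0.75 randomized per week).

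- *Cut-offs set at the planning values.* Requiring an observed rate of at least 25% and 40 patients within 53 weeks is met jointly by only about 43% of such trials (simulation). Also, 53 weeks is 371 days, while the plan itself implies 53.3 × 7 = 373 days.
- *Rate of at least 20%.* This means 40 randomized from at most 40 / 0.20 = 200 eligible patients: P(Bin(200, 0.25) ≥ 40) = 95.9%.
- *40 randomized within 80 weeks (1.5 × 53.3).* The expected number by then is 0.75 × 80 = 60: P(Poisson(60) ≥ 40) = 99.7%.
- *Slow recruitment is still detected.* At a true rate of 15% (assumed), the 20% cut-off is met with probability P(Bin(200, 0.15) ≥ 40) = about 3%.

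**The case against.** The strongest reply is that the label in the Objectives section is not the decision to proceed. Study timeline and status reserves that decision for a later review, and leaves single-centre or multi-centre open. Recruitment rate and time will be available to that review. This stands in part. A reader might infer from the rule that slow recruitment would lead directly to a mistaken decision to launch the main trial, and the document does not support that. But the review sets no recruitment criterion and does not alter the label, so the gap in the primary conclusion remains.

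A second reply is that recruitment may have been meant as descriptive, since Sample size treats it as a rate to be estimated with a confidence interval. The abstract says otherwise: feasibility is to be determined through all four measures.

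A third is that recruitment as slow as 133 or 267 weeks would be obvious long before any verdict. That is fair as a matter of practice, but the written rule gives nobody a basis for acting on it.

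A reader might also want to project how many years a main trial would take. That cannot be supported from this document. It states no design, endpoint, size or number of sites for the main trial, and the one-surgeon, one-centre setting describes the pilot. The 15% margin under Data monitoring serves only the pilot's interim check.

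**Conclusion.** The point holds as an inconsistency in the primary decision rule. Four outcomes are declared to determine feasibility, two are used, and no recruitment result can move the verdict out of the top tier. In size, recruitment at 2.5 or 5 times the planned duration gets the same label as recruitment on plan. This rests on the protocol's 3 eligible patients per week, on assumed rates of 10% and 5%, and on retention and completion both exceeding 80%.

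It should be fixed, but it is not critical. Randomization, the data and the estimates are unaffected, and the later review gives a chance to weigh recruitment. The finding is that the label can mislead, not that the protocol commits anyone to an infeasible trial.

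**What to change.** Before recruitment results are reviewed, amend the rule in the Objectives section as follows.

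1. Add recruitment rate and recruitment time, and let the overall verdict be the worst tier across the four measures.
2. State which planning rate is the benchmark, since Sample size uses both 25% and 33%.
3. Set the no-changes cut-offs below plan, so that a trial running to plan is rarely downgraded by chance. With 25% and 3 per week as benchmark, one example is an observed rate of at least 20% and 40 randomized within 80 weeks.
4. Define the lower tiers separately for each measure and without overlap, for instance feasible with changes (such as more sites) and infeasible. The lowest cut-off is the sponsor's choice. A single pair of limits joined by *or* should be avoided: at 10% recruitment the time is 2.5 times plan, so a middle tier of 10 to 25% or up to twice plan would put the trial in two tiers at once.

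The cost is protocol wording only, because both measures are already defined. The verdict becomes somewhat harder to pass. Under the example cut-offs, about 4% of trials running to plan would fall below the top tier on recruitment rate (100% − 95.9%), and well under 1% on time (100% − 99.7%).
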